**Techniques for evaluating isometric maximal voluntary force and muscle mass:**

- Microfet2: Measurement of the maximum voluntary force by a portable dynamometer: Microfet-2; Hogan Scientific. The measurement will be in a sitting position on a hard plane, without back support, on an examination table. The angle between the thigh and the leg will be 90 °. The measurement will be made 2 cm above the external malleolus. The length of the lever arm is defined by the distance between the tibial plateaus and the area of ​​attachment of the strap to the leg.

**-** Bioanalytical impedancemetry: Multifrequency impedance measurement of body composition: Body Composition Monitor (BCM); Fresenius Medical Care. The patient will be lying down at rest for at least 15 minutes after the end of the hemodialysis session.

- Creatinine index: A measure of daily creatinine production by the creatinine index estimated from anthropometric data (age, sex), dialysis dose (Kt / V urea) and pre-dialytic creatinine level. The creatinine index derives from modeling the kinetics of creatinine (10). This model is recognized as reflecting the muscle mass and nutritional status of HDC patients (10).

- Techniques for assaying the systemic parameters of the MIA syndrome:

Determination of creatinine of albumin and CRP: respectively by enzymatic method, immunonephelometry and immunoturbidimetry.

## Statistics:

### Expected number of people to be included in the study

Considering a linear multivariate model with 5 covariates (albumin - CRP - Voorrips score - LBM - creatinine index), a risk of the first species of 5%, a desired power of 90% and a force of the effect of 0, As proposed by Cohen (Cohen Behavioral Sciences 1988) it will be necessary to include 110 patients. The calculation was carried out on the software R 3.1.1 (R Coreteam, Vienna, Austria) package pwr.

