## Judgment criteria

### Main judgment criteria

In HDC patients, the multivariate analysis of the determinants of MVF (in Newton per meter): Muscle mass by impedancemetry and the Creatinine Index; the concentration of CRP and plasma albumin (MIA syndrome); physical activity by the Voorrips score.

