### Secondary endpoints

In patients with HDC:

- the linear correlation (Pearson) between the creatinine index and the MVF.

- the linear correlation (Pearson) between the lean mass estimated by impedancemetry and the MVF.

- the linear correlation (Pearson) between the Voorrips score and the MVF.

- linear correlation (Pearson) between plasma albumin concentration and MVF

- linear correlation (Pearson) between hemoglobin concentration and MVF

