# Expected Results and Outlook

**ORIGINALITY AND INNOVATIVE CHARACTER:**

The originality of this project is to jointly study the mass and muscle strength of patients on chronic hemodialysis (HDC). First, the assessment of muscle strength is based on a simple, fast, and non-invasive screening tool that will establish MVF values based on the age, weight, height, and sex of hemodialysis patients. chronic. Secondly, the evaluation of the muscular mass, delicate in hemodialysis because of the excess of extracellular water will be done by two complementary methods, by impedancemetry and by the creatinine index.

In the chronic hemodialysis patient, muscular dysfunction is a significant factor in morbidity and mortality and impairment of quality of life (17). Few studies have investigated the characterization of muscle dysfunction and the determinants behind these clinical abnormalities. In these patients, both lean body mass (LBM) loss of muscle mass (18) and impaired muscle function (19) are observed, leading to decreased exercise capacity (4). ). Inflammatory syndrome and oxidative stress in malnutrition-inflammation-atherogenesis (MIA) syndrome (20) are two important players in this muscle dysfunction (19) (21).

Prospective cohort of chronic hemodialysis patients: Evaluate, by prospective follow-up, the survival of chronic hemodialysis patients according to their strength and muscle mass.

Effort Retraining in Chronic Hemodialysis Patients: Evaluate the muscle strength and muscle mass of chronic hemodialysis patients after muscle reconditioning**.**

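### The primary model for maximal voluntary force omits age and sex, leaving the albumin and CRP (MIA) association open to confounding that the muscle-mass covariates absorb only in part

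*Protocol*

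**What the plan says.** Two places in the protocol fix the covariates of the primary regression, and they agree. The sample-size section (Expected number of people to be included in the study) reads "Considering a linear multivariate model with 5 covariates (albumin - CRP - Voorrips score - LBM - creatinine index". The Main judgment criteria name "Muscle mass by impedancemetry and the Creatinine Index", then "the concentration of CRP and plasma albumin (MIA syndrome); physical activity by the Voorrips score". Age and sex appear in neither list, and the statistical methods section adds only that multiple linear regression will be used.

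Other sections bear on the omission:

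- **Inclusion criteria.** Adults between 18 and 90 are eligible, with no restriction by sex.
- **Techniques section.** The creatinine index is "estimated from anthropometric data (age, sex), dialysis dose (Kt / V urea) and pre-dialytic creatinine level".
- **Expected Results and Outlook.** The strength measurement "will establish MVF values based on the age, weight, height, and sex of hemodialysis patients".
- **Secondary endpoints.** These are unadjusted correlations, among them "the linear correlation (Pearson) between the creatinine index and the MVF" and "linear correlation (Pearson) between plasma albumin concentration and MVF".

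No section states an adjustment for age or sex.

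**The concern.** The aim goes beyond description. The working hypothesis calls the MIA syndrome a determining factor, and the primary objective asks for its contribution to the fall in strength. Age is the obvious rival explanation: the Background itself introduces sarcopenia as a geriatric process. If older patients are weaker and also tend to have lower albumin or higher CRP, then albumin and CRP can be associated with MVF without contributing to it. Sex can act in the same way.

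The protocol expects MVF to be interpreted by age and sex, yet leaves both out of the model meant to identify the determinants of MVF. A significant albumin or CRP term from that model could not be separated from ageing. This is a list the protocol fixes twice and uses to size the study, so it is not a detail merely left open for the statistical analysis plan.

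**Working it through.** **1. The plan's own figure.** The protocol gives 5 covariates, alpha 5%, power 90% and N = 110. The effect size is cut off in the available text, so Cohen's medium f² = 0.15 is assumed. For the overall F test with u numerator and v denominator degrees of freedom, the noncentrality is λ = f²(u + v + 1) and N = u + v + 1.

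- With u = 5 and f² = 0.15, 90% power needs v = 109.47, so N = 116.
- At N = 110 (v = 104, λ = 0.15 × 110 = 16.5), power is 88.2%.
- The required N is 171 at f² = 0.10 and 89 at f² = 0.20.

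The stated 110 is thus close to, but not exactly, the N that f² = 0.15 implies. That is a separate matter.

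**2. How often the MIA test rejects with no true MIA effect.** The test taken is the joint test of albumin and CRP (2 df) at N = 110, the one that matches the primary objective. All correlations are assumed.

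One fully specified simulation used standardised age, sex coded ±1, a latent muscle factor m and independent standard normal errors e (2,000 replicates per row):

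- LBM = 0.5 sex − 0.2 age + 0.6 m + 0.5 e
- creatinine index = 0.4 sex − 0.4 age + 0.6 m + 0.5 e
- albumin = a·age + √(1 − a²) e
- CRP = −0.3 albumin + 0.95 e
- Voorrips = −0.3 age + 0.95 e
- MVF = b·age + 0.4 sex + 0.4 m + 0.2 Voorrips + 0.6 e

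| a (age on albumin) | b (age on MVF) | Planned 5 covariates | With age and sex |
|---|---|---|---|
| −0.2 | −0.2 | 4.6% | 4.2% |
| −0.2 | −0.4 | 6.5% | 4.7% |
| −0.3 | −0.2 | 5.0% | 4.1% |
| −0.3 | −0.4 | 9.1% | 5.0% |
| −0.4 | −0.2 | 4.7% | 4.9% |
| −0.4 | −0.4 | 14.0% | 5.3% |

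The Monte Carlo standard error near 5% is √(0.05 × 0.95 / 2000) = 0.5 percentage points.

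Other assumed loadings move the planned-model figure widely:

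- With age-albumin −0.2 to −0.4, age-CRP 0.1 to 0.2 and an age effect on MVF of −0.3 to −0.4 beyond mass, one set gave 9.3% to 27.8%, against 4.6% to 5.4% after adjustment.
- A set pairing age-albumin −0.2, −0.3 and −0.4 with age effects of −0.3, −0.35 and −0.4 gave 8%, 18% and 35%.
- A set with age-albumin −0.2, age-CRP 0.1 and age effect −0.3 gave 6.8%. It fell to 5.5% when the creatinine index tracked age at −0.7. The upper corner (−0.4, 0.2, −0.4) gave 21.8%.

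**3. The raw correlations, again on assumed values.**

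- *Albumin.* If albumin is linked to MVF only through age, the crude r is the product of the two age correlations. The low end is (−0.2)(−0.3) = 0.06 and the high end (−0.4)(−0.5) = 0.20. By Fisher's z with √107, these reach significance in about 10% and 56% of studies of 110.
- *Creatinine index.* If the index and MVF each correlate ρ in size with age and with sex, age and sex are uncorrelated and nothing else is shared, the induced r is 2ρ². This is 2 × 0.3² = 0.18 up to 2 × 0.5² = 0.50. The 5% critical value at N = 110 is 0.187.

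**4. Power after adding age and sex (N = 110).**

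| Test | 5 predictors (v = 104) | 7 predictors (v = 102) |
|---|---|---|
| MIA, 2 df, partial f² = 0.10, λ = f²(u + v + 1) | λ = 10.7, 83.1% | λ = 10.5, 82.3% |
| MIA, 2 df, partial f² = 0.10, λ = f²N | λ = 11.0, 84.2% | λ = 11.0, 84.1% |
| Overall F, f² = 0.15 | 88.2% | 83.3% |

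For the overall F test at 90% power and f² = 0.15, N goes from 116 to 130. The Recruitment potential section gives 110 as the number that can be included.

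**The case against.** The strongest reply is that the planned model already adjusts in part. The creatinine index contains age and sex, and lean mass reflects sex and body size. Where those two carry the signal well, or where age has little effect on strength beyond mass, the simulations show rejection at or near 5%. That stands, and it limits the claim. It does not remove it: the index mixes age and sex with Kt/V and creatinine, so how well it stands in for them is unknown.

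It can also be said that the statistical analysis plan, not shown, may add covariates. It may, but it would then depart from a list fixed in two sections of the protocol. Age and sex are not itemised under the parameters collected, but eligibility needs age and the creatinine index needs both.

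Three stronger readings are tempting, and the documents do not support them:

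- *That the MIA result is confounded, or its error rate inflated by a known amount.* No correlation of age or sex with albumin, CRP or MVF is given, so neither is established.
- *That the raw creatinine-index correlation is the wrong analysis.* The secondary objective asks how MVF relates to muscle mass as gauged by the index, and age and sex differences in mass belong to that relationship. The raw value answers it. It cannot show that the index carries information beyond age and sex, but the protocol does not ask that.
- *That height and centre must also enter the model.* These are reasonable preferences, not corrections of an error. With age, sex, height and a four-level centre factor (1 + 1 + 1 + 3 = 6 extra parameters), MIA power at partial f² = 0.10 would be 80.7%, and overall-F power at f² = 0.15 would be 74%.

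**Conclusion.** The point holds as an exposure to confounding in the primary analysis. The five-covariate model omits two variables that the protocol itself links to MVF and already needs for the creatinine index, in a cohort spanning ages 18 to 90. The direction of the risk and the remedy are clear; the size is not. Under assumed correlations with no true MIA effect, the planned 2-df test rejects from about 5%, which is no inflation, to about 28-35% in the most adverse cases. Adding age and sex brings it to about 5% in every set where the adjusted model was run. The power figures rest on assumed f² values, because the protocol's own effect size cannot be read.

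**What to change.** Add age and sex as fixed covariates to the primary regression, in both the Main judgment criteria and the sample-size section, before the database is locked. State that the primary conclusion rests on the adjusted albumin and CRP terms.

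As a supplement, report partial correlations adjusted for age and sex beside the raw Pearson values in the Secondary endpoints, and note that the creatinine index contains age and sex by construction. Height and centre are optional.

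The cost is two degrees of freedom and no new measurement. The MIA test loses under one percentage point of power at partial f² = 0.10. If the sample-size statement continues to refer to the whole model, its power at 110 patients should be restated with seven covariates. Stating power for the albumin and CRP test instead would match the primary objective and would not call for more patients than the centres can supply on that account.

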### Description of the planned statistical methods, including the schedule of planned interim analyzes

- Descriptive analysis and comparability of groups:

An initial descriptive analysis will be performed. For qualitative variables, this description will include the force. For quantitative variables, the description will include the size, mean, standard deviation, median, and extreme values by distribution.

- Analysis of the criteria of judgments:

The judgment criteria will be compared using a Student test. If the application conditions of the Student's test are not respected (normal distribution, equality of variances), a Mann-Whitney test will be used to compare these two groups.

Univariate correlations between the judgment criteria will be investigated using the Pearson or Spearman test, depending on whether or not the distribution of variables is normal. Multivariate analysis will be done by multiple linear regression.

A test will be considered significant when its degree of significance p is below the significance threshold of 5%.

Since no interim analysis is planned, a test will be considered significant when its degree of significance p is below the significance level of 5%. The analyzes will be carried out using the R version 2.13.0 software after the locking of the database and the approval of the Statistical Analysis Plan

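### The main-criterion regression tests lean mass and the creatinine index each with the other held fixed, so it can understate muscle mass as an adjusted determinant of MVF

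*Protocol*

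**What the plan says.** - **Model.** The protocol section on the expected number of people to be included sizes the study for a linear model with five covariates: "albumin - CRP - Voorrips score - LBM - creatinine index". It concludes that "it will be necessary to include 110 patients".
- **Main criterion.** Main judgment criteria makes the multivariate analysis of MVF determinants the criterion. It lists "Muscle mass by impedancemetry and the Creatinine Index" beside CRP, albumin and the Voorrips score.
- **Method.** The section on planned statistical methods says "Multivariate analysis will be done by multiple linear regression" and applies one 5% threshold to tests in general. It mentions no joint test of the two muscle measures.
- **What the two measures are.** Background introduces impedance and the creatinine index as the two bedside methods for assessing muscle mass. The section on parameters collected says the index reflects muscle mass and nutritional status. Expected Results and Outlook says the evaluation of muscle mass "will be done by two complementary methods, by impedancemetry and by the creatinine index".
- **Single-measure analyses.** Secondary endpoints lists a separate Pearson correlation with MVF for the creatinine index and for lean mass.

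**The concern.** With both measures in one model, the lean-mass coefficient asks whether lean mass adds anything once the creatinine index is known, and the reverse holds for the index. Neither coefficient asks whether muscle mass is a determinant of strength. If the two are well correlated, they share the effect between them and each standard error grows. Both can then miss 5%, or one can pass by chance, while the pair together clearly predicts MVF.

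This matters because muscle mass is one of the determinants named in the main criterion, and the protocol gives identifying the determinants of muscle strength as the study's expected result. A results table read coefficient by coefficient could understate muscle mass among the adjusted determinants.

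**Working it through.** **The plan's own figure.** The stated inputs are five covariates, "a risk of the first species of 5"% and "a desired power of 90"%. The effect size is cut off in the text ("a force of the effect of 0, As proposed by Cohen"), so 110 cannot be reproduced with certainty. If the conventional medium value f² = 0.15 is assumed, the overall 5-df F test needs 109.47 residual degrees of freedom, or N = 116, and N = 110 gives power 0.882. N = 110 gives 90% if f² is about 0.158. That is a separate matter. Here N = 110 is taken as given, with 110 − 5 − 1 = 104 residual degrees of freedom.

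**Inputs for the check**
- n = 110 and the five-covariate model (protocol).
- Correlation r between lean mass and creatinine index: not given; assumed 0.6, 0.7, 0.8.
- Standardised effect b of underlying muscle mass on MVF: not given for dialysis patients. Two values are used: 0.35 (assumed) and 0.51, the only strength-to-muscle correlation in the protocol (Background; muscle surface, healthy subjects).
- The two measures are equally good noisy readings of one latent muscle mass. The other three covariates are null and uncorrelated with them.

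**Formulas**
- Variance inflation: VIF = 1/(1 − r²) = 1.56 / 1.96 / 2.78.
- Squared correlation of each measure with MVF: c² = b²r.
- Both measures together: R² = 2c²/(1 + r).
- One coefficient given the other: f² = (R² − c²)/(1 − R²).
- The pair: f² = R²/(1 − R²).
- Noncentrality: 110 × f².

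**Worked case, b = 0.35, r = 0.7**
- c² = 0.1225 × 0.7 = 0.0858, and R² = 0.1715/1.7 = 0.1009.
- Single coefficient: f² = (0.1009 − 0.0858)/0.8991 = 0.0168; noncentrality 1.85; power about 0.27.
- Pair: f² = 0.1009/0.8991 = 0.112; noncentrality 12.3; power about 0.88.
- Simulation, which lets the covariates vary between studies, gives about 26% and 86%.

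**Simulated results, n = 110**

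| b | r | Neither coefficient significant | Joint 2-df test significant |
|---|---|---|---|
| 0.35 | 0.6 | about 42% | about 82% |
| 0.35 | 0.7 | about 49% | about 86% |
| 0.35 | 0.8 | about 60% | about 89% |
| 0.51 | 0.6 | 7 to 8% | over 99% |
| 0.51 | 0.7 | 10 to 12% | over 99% |
| 0.51 | 0.8 | 21 to 22% | over 99% |

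The ranges at 0.51 are the spread between separate simulation runs. At b = 0.35, exactly one coefficient is significant in a further 40 to 55% of studies. Because the two measures were generated as equally good, which one it is comes down to chance.

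**Sensitivity to how 0.51 is read.** If 0.51 is instead the correlation of each *measured* marker with MVF, neither coefficient is significant in only 0.1 / 1 / 9% at r = 0.6 / 0.7 / 0.8, rising to 43% at r = 0.9. With a marker correlation of 0.30 and r = 0.7, it is 47%, against joint power of 0.90.

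**Protection from the secondary endpoints.** In the same simulated studies at b = 0.35, both unadjusted correlations are non-significant in only about 4 to 8%.

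**The case against.** - **The primary objective is the contribution of MIA syndrome, that is CRP and albumin.** This stands. The precision of those coefficients depends on how well the remaining covariates together predict albumin and CRP, not on how strongly the two muscle measures correlate with each other. A reader might infer that the MIA test is compromised; the documents do not support that.
- **Muscle mass is already examined one measure at a time under Secondary endpoints.** This stands in part. Those correlations make it unlikely that a muscle-mass association would be missed altogether, so it goes too far to infer that the study would report none. They are unadjusted, however, and cannot replace an adjusted result of the kind the main criterion describes.
- **The two measures are not the same thing.** This stands. Background says lean mass includes organs, skin and bone, and that impedance is limited by excess extracellular water. It also says the creatinine index shifts with protein intake. The protocol calls the methods complementary. Entering both is defensible, and a model of two equally noisy readings of one quantity is a simplification.
- **The size depends on the assumed effect.** This stands. At 0.51 the loss is much smaller than at 0.35. The 0.51 comes from healthy subjects and muscle surface, so it does not settle the value for dialysis patients either.
- **The statistical analysis plan could add a joint test, and the 5% rule is a general one.** The plan is not shown and might do so. Nothing in the protocol says the coefficients must be read in isolation. But the protocol itself puts both measures in the main-criterion model and gives no other rule for judging them, so the correction belongs there.

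**Conclusion.** The point holds in a limited form. The main-criterion model tests each muscle-mass measure with an overlapping one held fixed, which is the wrong test for whether muscle mass is an adjusted determinant of MVF. Under the assumptions above, neither coefficient reaches 5% in about 42 / 49 / 60% of studies for an effect of 0.35, and in roughly 8 / 12 / 22% for 0.51. The loss is close to nil if each measured marker itself correlates 0.51 with MVF and r is 0.7 or less. The joint test keeps about 82 to 89% power at 0.35 and over 99% at 0.51.

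The true loss cannot be fixed from the protocol, which states neither the inter-measure correlation nor the effect in dialysis patients. The point concerns how the muscle-mass part of the main criterion is judged. It does not show that the MIA result is unreliable or that the two measures are interchangeable.

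**What to change.** In Main judgment criteria and in the sample-size section of the protocol:

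1. Keep the five-covariate model for the MIA question.
2. Judge muscle mass as a determinant by a 2-df F test comparing that model with and without lean mass and the creatinine index together.
3. Report each measure's adjusted coefficient from a model that contains only that measure, alongside albumin, CRP and the Voorrips score.
4. If coefficients from the joint model are shown, describe them as what one measure adds beyond the other, not as evidence for or against muscle mass.

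The cost is one extra F test, two extra model fits and a few lines of text. No new data or patients are needed, and the albumin and CRP analysis is unchanged.

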# Feasibility

## Recruitment potential

The number of subjects likely to be included is 200 patients. Indeed, the number of hemodialysis patients in the four investigative centers is 200 patients. The expected rate of patients not meeting the inclusion and non-inclusion criteria is 30%. The foreseeable rate of refusal to participate in the protocol is 15%. In total, a possible inclusion number of 110 chronic hemodialysis subjects.

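### If the effect size was Cohen's medium f² = 0.15, the stated 110 equals the residual degrees of freedom; 90% power needs 116 patients, and 110 give about 88% (minor)

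*Protocol*

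**What the plan says.** The protocol's section on the expected number of people to be included sets out the calculation. The model is described as "Considering a linear multivariate model with 5 covariates (albumin - CRP - Voorrips score - LBM - creatinine index"). The error rates are "a risk of the first species of 5%, a desired power of 90" per cent. The effect size appears as "a force of the effect of 0, As proposed by Cohen", so its digits are missing from the text available. The section concludes that "it will be necessary to include 110 patients" and names the tool: "The calculation was carried out on the software R 3.1.1 (R Coreteam, Vienna, Austria) package pwr".

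The section on recruitment potential starts from 200 haemodialysis patients in four centres. It expects 30% not to meet the criteria and 15% to refuse, and ends with "In total, a possible inclusion number of 110 chronic hemodialysis subjects". The expected inclusions therefore equal the stated requirement exactly.

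The analysis section plans a multiple linear regression, which matches the model used for sizing.

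**The concern.** For a linear model, pwr does not return a number of patients. It returns v, the denominator degrees of freedom of the F test, and the user must add the number of covariates u and 1 for the intercept. Reporting v as the sample size is an easy slip, and it understates the requirement by u + 1, which is six here. The stated 110 is what pwr gives for v at Cohen's medium effect. If that is what happened, the stated power and the stated size do not belong together. Because the recruitment section forecasts the same 110, the shortfall would not be absorbed by expected recruitment as written.

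**Working it through.** **Inputs from the protocol's sample-size section:** u = 5 covariates, α = 0.05, power 0.90, pwr, stated size 110.

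**Assumption:** f² = 0.15 (Cohen's medium value), because the printed value is not legible. A range is shown in step 3.

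**Formula (overall F test in a linear model, as in pwr):** power = P[F′(u, v, λ) > F₀.₉₅(u, v)], where F′ is noncentral F, λ = f²(u + v + 1) and N = u + v + 1.

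**Step 1. Reproduce 110.** With u = 5, α = 0.05, power 0.90 and f² = 0.15, the solution is v = 109.47, which rounds up to 110. The protocol's figure is reproduced as v. As a number of patients, N = 110 + 5 + 1 = 116.

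**Step 2. Power at the stated size.**

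| Complete patients N | v = N − 6 | λ = 0.15 × N | Power |
|---|---|---|---|
| 110 | 104 | 16.50 | 88.2% |
| 115 | 109 | 17.25 | 89.9% |
| 116 | 110 | 17.40 | 90.2% |

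The shortfall at 110 is 116 − 110 = 6 patients, or 90 − 88.2 = 1.8 power points.

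**Step 3. Dependence on the missing effect size (u = 5, power 90%).**

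| f² | v | N |
|---|---|---|
| 0.02 (Cohen small) | 823.03 | 830 |
| 0.14 | 117.30 | 124 |
| 0.15 (Cohen medium) | 109.47 | 116 |
| about 0.158 | 104 | 110 |
| 0.16 | 102.62 | 109 |
| 0.35 (Cohen large) | 46.90 | 53 |

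No conventional Cohen value gives N = 110.

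**Step 4. Other routes to 110.** At f² = 0.15, four covariates need 108 patients and six need 123. Reading the effect as R² = 0.13 gives f² = 0.13/0.87 and v = 109.89, so again N = 116. Reading it as R² = 0.15 gives N = 100. None of these gives 110 as a patient number.

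**Step 5. Incomplete records (illustrative rate, not from the protocol).** If 10% of 110 records lacked a value needed in the regression, 110 × 0.90 = 99 would remain, and power at f² = 0.15 would be about 84%.

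**Step 6. Recruitment forecast.** If both rates are shares of all 200 patients: 200 × (1 − 0.30 − 0.15) = 110. If refusal applies only to eligible patients: 200 × 0.70 × 0.85 = 119. The protocol's 110 matches the first reading. The second would cover 116 with three to spare; the first would not.

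**The case against.** The strongest objection is that the conclusion rests on a number nobody can read. The gap may come from translation or text extraction, so it is not itself an error in the plan, and raising f² from 0.15 to 0.158 makes the discrepancy vanish. This stands as a limit on certainty: a reader might take it as established that the protocol confused v with N, but the text supports only a strong inference. The inference is strong because pwr and Cohen are both named, the medium value returns 110 exactly as v, and no Cohen convention returns 110 as N.

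A reader might also infer that the study is underpowered for its primary question. The documents do not support that. The 88.2% is for the joint test of five covariates, whereas the primary objective concerns CRP and albumin. If 0.15 were the partial effect of those two in the five-covariate model, power at 110 would be about 95%. That partial effect is not given either, so neither figure is the power for the primary objective.

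A third tempting reading is that the absence of a missing-data margin is an error. The protocol gives no rate of incomplete records, there is no follow-up to lose patients from, and the 30% and 15% losses occur before inclusion. A margin would be sensible, but any rate is the reader's own assumption.

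Finally, a reader might say the recruitment arithmetic is wrong and should give 119. Applying refusal to eligible patients is the natural reading, but the base of the 15% is not stated, and 110 is correct if both rates refer to all 200.

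**Conclusion.** The point holds conditionally and is minor. On the assumption f² = 0.15, the stated 110 coincides with the residual degrees of freedom, the patient number for 90% power is 116, and 110 complete patients leave the overall five-covariate F test about 1.8 points short of its target. The assumption decides the result: below 0.15 the gap widens, and from about 0.158 upwards 110 is enough. A shortfall of this size in a one-time, minimal-risk cross-sectional study does not threaten the design. It is still worth correcting, because it concerns the number that fixes the study's size and the stated power probably does not match it.

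**What to change.** - In the sample-size section, confirm the effect size used and print it in full.
- If it is f² = 0.15, either keep 110 and restate power as about 88% for the overall F test with complete records, or state v = 110 and N = 116 for 90%.
- If incomplete records are to be considered, give the rate and label it an assumption.
- In the recruitment section, state the denominator of the 15% refusal rate. As a share of eligible patients it gives 119 expected inclusions, which covers 116. As a share of all 200 it gives 110, which does not.

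Keeping 110 costs only restated text and a slightly lower declared power. Moving to 116 means six more patients, within the same four centres' forecast only if refusal is counted among eligible patients.
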